### Statistical methods

2.18.

Generalized linear mixed models will be used to account for the correlation among youth from the same cluster as well as the correlation between observations from the same youth. Descriptive statistics will be used to summarize the sample with regard to baseline characteristics of interest. Means and standard deviations will be presented for continuous variables, while sample proportions will be provided for categorical variables. 95% confidence intervals will accompany all sample statistics. Primary assessment of intervention effects will be based on intent-to-treat estimates. As-treated, or treatment-on-the-treated (TOT), effect parameters will be estimated in secondary analyses and reported as exploratory. Between-site differences regarding intervention effects will be assessed based on level of staff/facilitator engagement in curricular delivery as well as other observed external factors that may interact with the intervention to alter outcomes. SAS software will be used for all statistical analyses.

To assess differences at baseline between the youth in the experimental and control groups, demographics such as grade-level, race, nativity, and parental education will be compared while accounting for within-neighborhood clustering. Demographic variables as well as neighborhood-level characteristics resulting in between-arm imbalances will be considered as covariates in the primary and secondary analyses.

Participation bias will be assessed by comparison of age and race/ethnicity of youth participating in the study compared to the overall demographics of adolescents (school district and census data). Significant differences detected via chi-square analysis will be noted as potential validity threats.

An attrition analysis will be conducted by comparing youth who completed follow-up surveys with those who did not with regard to demographics as well as outcomes measured at baseline. All hypotheses will be two-sided tests with a significance level of 5%.

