Following Twisk and Proper’s recommendations for randomized controlled trials with both baseline and follow up measures (in this case abuse perpetration) [100], we will also construct multinomial logistic regression models that account for presence or absence of baseline perpetration. That is, we will examine intervention effects among youth reporting baseline SV/ARA perpetration and the likelihood of becoming ‘non abusive’ at follow up (i.e., an ‘early intervention’ effect). Similarly, we will examine intervention effects among youth with no baseline SV/ARA perpetration and the likelihood of ‘staying non abusive’ (i.e., a primary prevention effect). We have used this approach to analyze intervention effects on abuse exposure in our school health center relationship abuse prevention study [101].

We will also conduct two sets of exploratory analyses. First, we will conduct an intensity-adjusted analysis that reflects the actual delivery of the program. To achieve this, we will use a continuous score of “intensity” to replace the binary intervention variable in the models for the primary analysis. This score will be calculated for each round (program delivery) by using two sources of information. The first is information collected systematically about each session by trained research assistants who observed the sessions, including whether each task assigned to a module was performed (yes or no). The second is a summary measure of overall attendance for each round, tracked by using sign-in sheets with the research assistants. The second set will be a per-protocol analysis. This set of models will include only participants in the intervention arm that received the full intervention, defined as having covered a minimum threshold of tasks across the six sessions and having sufficient attendance. These measures replicate the intensity score values, but are then dichotomized to yes or no to receiving the full intervention. All control arm participants will be included in these models.

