To explore whether demographics, youth pre-intervention risk and protective factors (e.g., history of SV/ARA exposure, sexual risk, connectedness), and site-level differences (e.g., staff experience, organizational capacity, intervention intensity) moderate the effect of the intervention on the primary and secondary outcomes, linear mixed models slightly different from those described above will be utilized. The outcome variables will be modeled as a function of the following variables: the outcome at baseline, the treatment group, the potential moderator, the interaction between the treatment group and moderator, and a random effect for cluster. A significant interaction suggests the presence of intervention effect heterogeneity, and we will follow the approach of Kraemer [102] by focusing on effect size derivation rather than formal hypothesis testing.

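### Intervention intensity is listed as an effect moderator, but it arises after randomisation and partly measures a different curriculum in each arm, so its interaction with arm cannot be read as effect modification

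*Protocol article*

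**What the plan says.** All the analysis statements are in section 2.18 (Statistical methods) of the protocol article.

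- **Moderators.** The plan will explore whether site-level differences, with "staff experience, organizational capacity, intervention intensity" as the examples, alter the intervention effect on primary and secondary outcomes. The model contains the baseline outcome, treatment group, "the potential moderator, the interaction between the treatment group and moderator, and a random effect for cluster".
- **Planned reading.** "A significant interaction suggests the presence of intervention effect heterogeneity", with the emphasis on "focusing on effect size derivation rather than formal hypothesis testing".
- **What intensity is.** In the exploratory intensity-adjusted analysis, intensity is a continuous score that takes the place of the arm variable. "This score will be calculated for each round (program delivery"), from two sources: research assistants' records of whether the tasks of each module were carried out, and a summary of attendance.
- **Facilitator engagement.** Separately, "Between-site differences regarding intervention effects will be assessed based on level of staff/facilitator engagement in curricular delivery", together with other observed external factors. No model is given for this.

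**The concern.** An interaction between arm and moderator describes variation in a treatment effect when the moderator is fixed before allocation, or at least cannot be altered by it, and means the same thing in both arms. Site type or a baseline youth factor qualifies. A score made from how sessions went and who attended does not. It is partly a result of the allocated programme and partly a marker of which young men kept coming.

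The risk is one of interpretation. If rounds with good attendance enrol lower-risk youth, and this link is stronger in one arm than in the other, the model returns an interaction even when the programme effect is the same everywhere or absent. The natural reading would be that the programme works where it is well delivered. That bears directly on the implementation questions that the Discussion says the trial will explore.

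**Working it through.** **Step 1. Is intensity measured after randomisation?** Yes. Section 2.16.2 places randomisation after a site in a new neighbourhood had been approved. Both parts of the score come from sessions held later. In the moderator paragraph, the condition that a factor be pre-intervention is attached to the youth risk and protective factors and not to the site-level items. Nothing else in the article limits moderators to characteristics fixed before allocation.

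**Step 2. Does it mean the same thing in both arms?**

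| Component | Intervention arm | Control arm |
|---|---|---|
| Tasks completed | Gender, violence, and sexual and reproductive health (2.6) | First six job-skills modules (2.7) |
| Attendance | Tracked at every session (2.5) | Tracked at every session (2.5) |
| Schedule | Variants in 2.5, except the three-day summer format | Same variants, plus that format |

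Attendance is recorded in the same way in both arms. Task completion is not the same quantity.

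**Step 3. What score do control rounds take?** The article does not say. There are two possibilities:

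- *Control rounds scored zero*, which substituting the score for the arm variable might imply. With arm A (1 or 0) and intensity M, A × M = M in the intervention arm because A = 1, and A × M = 0 = M in the control arm. The columns for M and A × M are identical, so the interaction cannot be estimated separately from intensity.
- *Control rounds scored on their own curriculum.* The interaction can then be estimated, but it compares slopes on two differently defined scores.

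**Step 4. Size under assumed values (risk-difference scale).** The plan states no figure to reproduce. Assume no programme effect, with perpetration of 15% in high-intensity and 25% in low-intensity intervention rounds. Vary only the gradient across control rounds:

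| Control, high / low | Difference in high rounds | Difference in low rounds | False contrast |
|---|---|---|---|
| 15% / 25% | 15 − 15 = 0 | 25 − 25 = 0 | 0 points |
| 17.5% / 22.5% | 15 − 17.5 = −2.5 | 25 − 22.5 = +2.5 | 5 points |
| 20% / 20% | 15 − 20 = −5 | 25 − 20 = +5 | 10 points |

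With equal numbers of high and low rounds, every arm averages 20%, so there is no overall effect in any row.

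**Step 5. Simulation under assumed values.** The set-up was 11 intervention and 10 control clusters (section 2.16.1), the same arm effect in every cluster, and a latent site factor with effect b on the outcome. Intensity was standardised and correlated r1 with that factor in the intervention arm and r0 in the control arm. Cluster-level least squares was used, with a two-sided 5% test and 4,000 runs. In this set-up the slope of outcome on intensity is b × r in each arm, so the expected false interaction is b × (r1 − r0). For example, −0.3 × (0.7 − 0.2) = −0.15. Ranges are for b = −0.3 and b = −0.5, in arbitrary outcome units.

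| r1, r0 | Mean interaction | Share significant |
|---|---|---|
| 0.5, 0.5 | about 0 | about 5% |
| 0.7, 0.2 | −0.15 to −0.24 | 8% to 11% |
| 0.8, 0 | −0.24 to −0.39 | 14% to 23% |
| 0.9, 0 | −0.27 to −0.46 | 17% to 30% |

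The distortion is in the estimate itself, so preferring effect sizes to tests does not remove it.

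**The case against.** The best defence is that this is an exploratory analysis, framed around effect sizes, in a trial whose primary assessment is intent-to-treat and does not use the intensity score. Equal tracking of site risk in both arms would leave the interaction unbiased, and the documents do not show that tracking is unequal. Scoring details may sit in a fuller plan. All of this stands and keeps the point minor. It does not rescue the stated reading, because nothing in the article makes equal tracking something one could rely on.

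Several stronger readings are tempting, and the documents do not support them:

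- *That an interaction between arm and facilitator engagement is planned.* Section 2.18 says only that between-site differences in effect will be assessed "based on level of staff/facilitator engagement in curricular delivery". It states no interaction model and does not say whether control sites enter.
- *That control rounds are scored on job-skills tasks.* Section 2.5 shows that fidelity and attendance were recorded in both arms, but no text says what intensity score a control round receives.
- *That high-intensity intervention rounds have no comparable control rounds.* Attendance was tracked in both arms, and the control programme was matched at 18 hours and six modules. Only the task component differs in content.
- *That the analysis produces a false 10-point difference, larger than the 8.3-point design difference.* The 10 points follow from assumed rates at the unfavourable end. The 8.3 points in section 2.12 are a detectable main effect, not an interaction contrast.

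**Conclusion.** The concern holds in a limited form. Intervention intensity, as the article defines it, is a post-randomisation measure whose task component refers to different curricula by arm, and the score for control rounds is not stated. Its interaction with arm therefore cannot be read as heterogeneity of the intervention effect.

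The possible distortion runs from none to 10 points in the assumed-rate illustration. In the simulation, the share of falsely significant interactions runs from about 5% to 30%. Every rate and correlation behind these ranges is an assumption. The upper values require intensity to track site risk in the intervention arm and not at all in the control arm. The different curricula make some inequality plausible, but the documents cannot establish it.

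This rests on taking intensity in the moderator list to be the score defined in the intensity-adjusted analysis, the only definition the article gives. Staff experience and organisational capacity are not faulted as such. They are sound moderators if recorded before allocation, which the article does not state. The consequence is confined to exploratory results.

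**What to change.** 1. Remove intervention intensity from the moderator list in section 2.18.
2. State that models with an arm-by-moderator term use only characteristics recorded before allocation. Keep staff experience and organisational capacity only if they were so recorded.
3. Report intensity, and the facilitator engagement named earlier in section 2.18, as descriptive, non-randomised associations within the intervention arm.
4. Label the intensity-adjusted analysis as non-randomised too, since the same confounding by delivery and attendance applies there, and state the score given to control rounds.

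The cost is one exploratory contrast, a few sentences of text, and possibly a second site-level moderator if its timing cannot be documented. The within-arm associations will rest on 11 clusters. The Discussion notes that dose is known only by round, so individual-level modelling cannot replace what is dropped. The primary analysis and the sample size do not change.

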### Monitoring

2.19.

#### Data monitoring

2.19.1.

Given the sensitivity of the questions being asked regarding violence perpetration, we received a Certificate of Confidentiality from the Centers for Disease Control and Prevention to protect the research data from subpoena. Extra precautionary measures were taken to protect the data, including the use of a personally created ID code to maintain anonymity of the survey data and an internal data safety and monitoring plan, which included the following:
a)Systematically review assessment materials to ensure that assessment is conducted appropriately and that participants disclosing abuse or violence during the course of taking the survey receive appropriate connection to violence-related services and that mandated reports are made by site personnel when appropriate.b)Systematically review notes from research assistants to ensure that participants experiencing distress are being connected directly with the site directors and youth workers, receiving educational materials, and being referred appropriately; this includes ensuring that all research assistants document asking each participant about emotional distress after completion of the survey.c)Monitor staff performance with regard to protection of privacy, confidentiality, maintenance of secure data bases, and study procedures designed to reduce the risk of distress and potential breaches of confidentiality.d)Ensure that the PI ([name]), or a designated qualified individual, will be available by pager in case research staff needs to confer regarding participants’ behaviors or comments made during a survey or other research activities.e)Ensure that the PI ([name]), or a designated qualified individual, will be available by pager in case educators or violence prevention advocates from Center for Victims and Pittsburgh Action Against Rape, needs to confer regarding participants’ or youth workers’ behaviors or comments made during study implementation (i.e., during training, survey administration, or follow up contact with site administrators, youth workers and facilitators).f)Review and report any adverse events associated with the study.

## Results

3.

Related to recruitment, at least one site from the 21 neighborhoods agreed to participate (Fig. 3). Eleven neighborhoods were allocated to the experimental condition and ten to the control condition, and the neighborhood characteristics were similar between intervention and control neighborhoods (Table 3). There were a total of 866 age-eligible male youth who attended the program (464 in the experimental group; 402 in the control); all 866 enrolled in the study and completed a baseline survey (100% participation).

As detailed in Table 3, most participants (70%) identify themselves as Black or African American and 88% were born in the US. Participants’ age ranges overall were roughly evenly divided across 13–14, 15–16, and 17–19; the intervention arm had a slightly lower proportion of 13–14 year olds and higher proportion of 15–16 year olds compared to the control arm. At the time of their baseline survey, 22% were in middle school and 62% were in high school.

Compared to the control arm, the intervention group had higher proportions of those who self-identified as White, Multiracial, or Other racial category, and lower proportions of those who self-identified as Black/African American or Hispanic. Intervention and control arm participants were similar in all other characteristics.

## Discussion

4.

“Manhood 2.0” is a gender transformative curriculum adapted from the international setting that involves critical reflections, challenging of, and ultimately transforming, harmful gender and sexuality norms that foster violence against women and seeks to promote bystander intervention (i.e., giving boys skills to interrupt abusive behaviors they witness among peers) to reduce the perpetration of sexual violence (SV) and adolescent relationship abuse (ARA). This is a community-based cluster-randomized controlled trial in lower resource, Pittsburgh neighborhoods that involves high school age adolescent males to test the effectiveness of Manhood 2.0. The comparison intervention is a job readiness training program which focuses on skills needed to prepare youth for entering the workforce, including goal setting, accountability, resume building, and interview preparation. The primary outcome of interest is whether Manhood 2.0 reduces SV/ARA perpetration at Time 3 (9 months after program). Increases in positive bystander behaviors (i.e., intervening in a peer’s disrespectful or harmful behavior) is a secondary outcome. Other related intermediate outcomes are changes in recognition of what constitutes abusive behavior, intentions to intervene, and gender equitable attitudes.

Strengths of this study are the rigorous approach using a cluster-randomized controlled trial design combined with strong partnerships with multiple community partners including community leaders, youth serving agencies, churches, libraries, and school districts who facilitate recruitment and retention. Additionally, close attention to fidelity to intervention will allow for exploratory analyses about implementation: organizational and facilitator-level characteristics that contribute to high fidelity to the intervention; strategies community facilitators use for introducing and facilitating discussions; and barriers and facilitators for intervention implementation.

The study also has several limitations. The surveys are collected anonymously with each participant creating their own personal identification code that only they will know to match surveys over time. Thus, the dosage of program received (i.e., proportion of program completed) can only be calculated at the level of each round rather than at the individual level. As a community-based study recruiting youth who are at high risk for school ‘push out,’ retention of this cohort remains a critical challenge, with the most vulnerable at especially high risk for being lost to follow up. Additionally, youth who are juvenile justice system-involved are particularly difficult to retain. Thus, we are likely to have significant missing data from rounds involving justice system-involved youth. We will conduct sensitivity analyses both with and without these youth in the sample to examine differences in intervention effects.

In summary, this study protocol is intended to evaluate Manhood 2.0 using a rigorous design to determine the effectiveness of a community-based sexual violence and adolescent relationship abuse prevention program for high school age youth living in low resource neighborhoods. Findings may provide urgently needed information about the effectiveness of a gender transformative program that combines healthy sexuality skills, gender norms change, and bystander skills to interrupt peers’ disrespectful and harmful behaviors to reduce SV/ARA perpetration among adolescent males.

## Figures and Tables

**Fig. 1. F1:**
[figure not shown]
Conceptual model for Program H.

**Fig. 2. F2:**
[figure not shown]
Manhood 2.0: engendering healthy masculinities – study flow.

**Fig. 3. F3:**
[figure not shown]
CONSORT diagram.

**Table 1: T1:** Neighborhood characteristics.

Neighborhood	Non-white students	Economically Disadvantaged^a^	Student stability rate^b^	Graduation rate^c^	Chronic Absenteeism^d^	School Suspension^e^
Control (median)	84%	80%	81%	81%	56%	30%
Allentown/Beltzhoover/Hilltop*	45%	66%	83%	86%	43%	23%
Clairton^†^	81%	99%	n.a.	79%	n.a.	n.a.
Garfield*	95%	81%	81%	81%	56%	31%
Hazelwood*	52%	40%	88%	88%	28%	12%
Hill District*	95%	81%	81%	81%	56%	31%
North Braddock^†^	65%	100%	n.a.	83%	n.a.	n.a.
Northside*	87%	79%	70%	72%	69%	30%
Northview*	87%	79%	70%	72%	69%	30%
Downtown*	64%	67%	88%	92%	13%	23%
Wilkinsburg*	99%	80%	72%	77%	66%	36%
**Intervention (median)**	**52%**	**64%**	**72%**	**84%**	**66%**	**36%**
Duquesne^†^	35%	45%	n.a.	93%	n.a.	n.a.
East Hills*	52%	40%	88%	88%	28%	12%
East Liberty*	99%	80%	72%	77%	66%	36%
Homewood*	99%	80%	72%	77%	66%	36%
Larimer*	99%	80%	72%	77%	66%	36%
McKeesport^†^	51%	100%	n.a.	85%	n.a.	n.a.
Munhall^†^	38%	56%	n.a.	97%	n.a.	n.a.
Penn Hills^†^	67%	61%	n.a.	84%	n.a.	n.a.
Prospect Park^†`^	16%	33%	n.a.	94%	n.a.	n.a.
Sheraden*	64%	64%	85%	78%	36%	17%
Wilmerding^†^	41%	100%	n.a.	79%	n.a.	n.a.
Kolmogorov-Smirnov two-sample exact test comparing intervention and control, *p*-value	0.3230	0.1088	0.8695	0.5783	0.8695	0.2945

n.a. indicates data were not available for the neighborhood school district.

* Reference [103].

† Reference [104].

a Economically disadvantaged: Students are identified as economically disadvantaged based on the state’s Direct Certification process, which can include poverty data sources such as the Supplemental Nutrition Assistance Program, Transitional Assistance for Families with Dependent Children, or Medicaid eligibility; and children living in foster care.

b Student stability rate: total number of students who didn’t transfer during the entire year divided by the official enrollment for that year, which is calculated in October.

c Graduation rate: rate of individual 9th graders in 2012 who graduated in 2016 or earlier.

d Chronic absenteeism: the percentage of students who were absent 10% or more of the days they were enrolled in the school.

e School suspension: percentage of students who were suspended (out-of-school suspensions only) at least once during the school year.

**Table 2 T2:** Individual youth-level outcome measures.

Construct	Response options	Surveys				Items
	Primary Outcome: Any Sexual Violence/Adolescent Relationship Abuse Perpetration (comparing differences between intervention and control at Time 3)					
Physical/sexual IPV [79]	Yes/no to each Modeled as yes to any lifetime (baseline only) and yes to any past 9 months	X			X	*Have YOU done any of the following to someone you were in a relationship with (like he or she was your partner/girlfriend/boyfriend, you were dating or going out with, them) or hooking up with:* 1. …[ever/in the past 9 months] hit, pushed, slapped, choked or otherwise physically hurt someone you were going out with or hooking up with? (include such things as hitting, slamming into something, or injuring with an object or weapon.) 2. …[ever/in the past 9 months] used physical force or threats to make someone you were going out with or hooking up with have sex (vaginal, oral, or anal sex) when they didn’t want to? 3. … [ever/in the past 9 months] had sex with someone you were going out with or hooking up with when they didn’t want to or because you made them feel like they didn’t have a choice (even though you did not use physical force or threats)?
Dating abuse [37]	Baseline - No, I have never done this to someone I was in a relationship with - Yes, I have done this in the past 9 months - Yes, I have done this, but not in the past 9 months T3: Yes/no Modeled as summary score for lifetime (baseline only) and past 9 months	X			X	*Have YOU done any of the following to someone you were going out with (like he or she was your partner/girlfriend/boyfriend, you were dating them) or hooking up with:* 1. Spread rumors about their sexual reputation, like telling people they’re ‘easy’. 2. Convinced them to have sex, after they had said no a few times. 3. Made them have sex when they didn’t want to. 4. Physically hurt them (like shoving, grabbing, slapping, punching, choking). 5. Threatened to hurt them if they didn’t do what you wanted them to do. 6. Yelled at them or destroyed something that belonged to them. 7. Called them names, like ugly or stupid. 8. Told them not to talk to others or told them who they could hang out with. 9. Showed friends or posted pictures of them naked or doing something sexual. 10. Talked about what you and your partner do sexually with your friends or peers.
Non-partner sexual violence [79]	Yes/no to each Modeled as yes to any lifetime (baseline only) and yes to any past 9 months	X			X	*Now think about experiences you may have had with people who you were NOT going out with or hooking up with (this could include strangers, friends, family, or people you don’ know well).* *Please tell us whether YOU have [ever/in the past 9 months] done these things to anyone you were NOT going out or hooking up with:* 1. …used physical force or threats to make someone you were not going out with or hooking up with have sex (vaginal, oral, or anal sex) with you when they didn’t want to? 2. …insisted that someone you were not going out with or hooking up with have sex (vaginal, oral, or anal sex) when they didn’t want to, without using force or threats?
Sexual harassment [82,83]	4 point scale for frequency: never/a few times/once or twice a week/every day or almost every day Modeled as a summary score of responses of “a few times” or more often	X			X	*In the past 9 months since [insert month], how often have you done the following things to someone when they did not want you to?* 1. Made unwelcome sexual comments, jokes, gestures, or looks? 2. Showed, gave, or left sexual pictures, drawings, messages, or notes? 3. Spread sexual rumors about them? 4. Touched, grabbed, or pinched them in a sexual way? 5. Forced them to kiss you?
Cyber sexual abuse [3,84,85]	4 point scale for frequency: never/a few times/once or twice a week/every day or almost every day Modeled as yes for any response of “a few times” or more often	X			X	*In the past 9 months since [insert month], how often did you do the following to someone? How often did you…* 1. …try to get them to talk about sex when they did not want to… 2. …ask them to do something sexual that they did not want to do… 3. …post or publicly share a nude or semi-nude picture of them… …using mobile apps, social networks, texts, or other digital communication?
Incapacit-ated sex [80]	Yes/no	X			X	In the past 9 months since [insert month], have you done something sexual with someone when they were too drunk or high to stop you (this can include kissing, touching, fingering them, or having intercourse)?
Use of alcohol or drugs on purpose [81]	Yes/no	X			X	In the past 9 months since [insert month], have you given someone alcohol or drugs on purpose so you could do something sexual with them (this can include kissing, touching, fingering them, or having intercourse)?
		**T1**	**EOP**	**T2**	**T3**	
	**Secondary Outcomes: bystander behaviors, intentions to intervene, gender attitudes, recognition of abusive behavior, condom and contraceptive self-efficacy (differences between intervention and control at Time 2 and Time 3)**					
Positive bystander intervention behaviors [37]	I have not experienced this in the past 3 months. (0) I didn’t say anything. (−1) I told the person in public that acting like that was not okay. (+1) I laughed or went along with it (−1) I told the person in private that acting like that was not okay. (+1) I talked to an important adult about it privately (like youth leader, teacher, coach). (+1) Sum items with at least 1 positive response behavior (noted as +1) endorsed	X		X	X	*The following questions ask about specific behaviors that you may have seen or heard among your male peers or friends. If you experienced this at least once in the past 3 months, how did you respond?* 1. Making rude or disrespectful comments about a girl’s body, clothing, or make-up. 2. Spreading rumors about a girl’s sexual reputation, like saying “she’s easy.” 3. Telling sexual jokes that disrespect women and girls. 4. Bragging about what they and their girlfriend do sexually. 5. Showing other people sexual messages or naked/sexual pictures of a girl on a cell phone or the internet. 6. Doing unwelcome or uninvited things toward a girl (or group of girls) such as howling, whistling, or making sexual gestures. 7. Fighting with a girl where he’s starting to cuss at or threaten her. 8. Taking sexual advantage of a girl (like touching, kissing, having sex with) who is drunk. High from drugs, or passed out. 9. Shoving, grabbing, or otherwise physically hurting a girl.
Condom negotiation self-efficacy [86]	5 point Likert scale from ‘strongly disagree’ to ‘strongly agree,’ modeled as a mean score	X		X	X	1. I feel confident in my ability to discuss condom use with any partner I might have. 2. I feel confident in my ability to suggest using condoms with a new partner. 3. If I were to ask my partner to use a condom, I would be afraid that my partner would be upset with me. *(reverse coded)* 4. If I were unsure of my partner’s feelings about using condoms, I would not ask my partner to use one. *(reverse coded)* 5. If my partner didn’t want to use a condom during sex, I feel confident in my ability to refuse to have sex.
Attitudes related to condom and contraceptive use [87–90]	5 point Likert scale from ‘strongly disagree’ to ‘strongly agree,’ modeled as a mean score	X		X	X	*Please rate the following statements from Strongly Disagree to Strongly Agree:* 1. Using birth control keeps your partner from worrying about getting pregnant. 2. Using birth control gives you a sense of control. 3. Using birth control is too much trouble or too much of a hassle to use. 4. Using birth control takes too much planning ahead of time to have birth control on hand when you’re going to have sex. 5. Using birth control lets you have sex without worrying about getting your partner pregnant. 6. Using birth control makes sex feel unnatural. 7. Using birth control makes sex less exciting. 8. It does not matter whether you use birth control or not; when it’s your time to get pregnant, it will happen. 9. It is mainly a girl or woman’s responsibility to make decisions about birth control. 10. I am in favor of my partner and me using birth control.
Recognition of ARA [91]	5 point Likert scale from ‘not abusive’ to ‘extremely abusive,’ modeled as a mean score	X		X	X	*Please rate each of the following actions towards a girlfriend or boyfriend as not abusive, a little abusive, somewhat abusive, very abusive or extremely abusive.* 1. Name calling or insulting them. 2. Telling them they’re ugly or stupid. 3. Making fun of them in front of other people. 4. Telling them what to do all the time. 5. Telling them which friends they can and can’t see or talk to. 6. Pressuring them not to break up with them. 7. Not listening to what they have to say. 8. Trying to convince them to have sex. 9. Preventing them from leaving a room. 10. Keeping tabs on them or spying on them. 11. Threatening to hit them. 12. Forcing them to have sex.
Gender-equitable attitudes [37,92,93]^a^	5 point Likert scale from ‘strongly disagree’ to ‘strongly agree,’ modeled as a mean score	X		X	X	*Please rate the following statements from strongly disagree to strongly agree.* 1. A guy takes responsibility for his actions. 2. A guy never needs to hit another guy to get respect. 3. A girl wearing revealing clothing deserves to have comments made about her.^b^ 4. It bothers me when a guy acts like a girl.^b^ 5. Guys should sleep with as many girls as possible.^b^ 6. If a guy tells people his worries, he will look weak.^b^ 7. In a good dating relationship, the guy gets his way most of the time.^b^ 8. Guys should only have sex with girls.^b^ 9. I can respect a guy who backs down from a fight. 10. I would be friends with a guy who is gay. 11. A guy should share in household chores. 12. If a girl is raped it is often because she did not say “no” clearly enough.^b^ 13. Guys put women and children first.
Intentions to intervene with peers [37]	5 point Likert scale from ‘very unlikely’ to ‘very likely,’ modeled as a mean score	X		X	X	*How likely are YOU to do something to try and stop wha’s happening if a male friend or peer (someone your age) is:* 1. Making rude or disrespectful comments about a girl’s body, clothing or make-up. 2. Spreading rumors about a girl’s sexual reputation, like saying “she’s easy”. 3. Fighting with a girl where he’s starting to cuss at or threaten her. 4. Doing unwelcome or uninvited things toward a girl (or group of girls) such as howling, whistling or making sexual gestures. 5. Shoving, grabbing, or otherwise physically hurting a girl. 6. Showing other people sexual messages or naked/sexual pictures of a girl on a cell phone or the internet. 7. Telling sexual jokes that disrespect women and girls. 8. Taking sexual advantage of a girl (like touching, kissing, having sex with) who is drunk, high from drugs, or passed out.

ID, investigator-developed.

a Formative research was used to create this scale with NICHD R24HD080194.

b Items were reversed coded.

**Table 3 T3:** Baseline characteristics of participants.

Demographics	Total (n=866) % (n)	Treatment arm		p-Value^a^
		Intervention (n = 464) % (n)	Control (n = 402) % (n)	
Age (years)				0.0707
13–14	32.3 (280)	28.5 (132)	36.8 (148)	
15–16	39.0 (338)	42.5 (197)	35.1 (141)	
17–19	28.4 (246)	28.9 (134)	27.9 (112)	
Race				0.0075
Black/African American	70.3 (609)	68.1 (316)	72.9 (293)	
White	3.4 (29)	4.7 (22)	1.7 (7)	
Hispanic	6.1 (53)	3.5 (16)	9.2 (37)	
Multiracial	6.4 (55)	8.0 (37)	4.5 (18)	
Other	8.1 (70)	10.3 (48)	5.5 (22)	
Born in the United States				0.6619
Yes	87.5 (758)	88.2 (409)	86.8 (349)	
No	5.7 (49)	6.7 (31)	4.5 (18)	
Education status				0.3406
Currently in school	84.8 (734)	85.8 (398)	83.6 (336)	
Not in school – completed high school degree	3.2 (28)	3.0 (14)	3.5 (14)	
Not in school – did not complete high school degree	4.9 (42)	4.1 (19)	5.7 (23)	
Current grade level^b^				0.3691
8th	22.2 (163)	18.8 (75)	26.2 (88)	
9th	24.5 (180)	25.1 (100)	23.8 (80)	
10th	20.4 (150)	21.9 (87)	18.8 (63)	
11th	17.7 (130)	18.8 (75)	16.4 (55)	
12th	9.8 (72)	11.1 (44)	8.3 (28)	
College	0.8 (6)	0.5 (2)	1.2 (4)	
Parents’/guardians’ highest education				0.7656
Did not complete high school	43.7 (378)	41.8 (194)	45.8 (184)	
Completed high school or GED	17.2 (149)	17.0 (79)	17.4 (70)	
Some college	7.6 (66)	7.5 (35)	7.7 (31)	
College degree or higher	24.0 (208)	25.9 (120)	21.9 (88)	

a Wald log-linear chi square, accounting for clustering.

b Among those who reported currently being in school.
